## Abstract

**Background:**

In an increasingly older adult population, understanding the inter-relationship between three age related conditions malnutrition, frailty and sarcopenia is important in order to improve their recognition, treatment and prevention. This study aims to determine the overlap between malnutrition, frailty and sarcopenia by measuring estimates of prevalence for each individual condition. In addition, we will compare two models of frailty which are the accumulation of deficits and phenotype models.

**Methods/design:**

This is a cross-sectional study that will use the UK Biobank database, which will include a subset of 381,000 participants: males and females aged 50 years and above who completed the baseline assessments. For the baseline assessments, details of the participants’ characteristics will be included. All three conditions will be identified and mapped to variables collected at the baseline assessment. Variables for malnutrition will be mapped according to the Global Leadership Initiative on Malnutrition (GLIM) criteria. Frailty will be defined according to two models: the 36 deficits and the phenotype model. Finally, sarcopenia will be assessed according to the European Working Group on Sarcopenia in Older People (EWGSOP) standard.

**Discussion:**

This proposed study will help to understand the presence of malnutrition, frailty and sarcopenia in the older population and describe any overlap between the conditions. There is little published research on the overlap between these three conditions. Despite the similarity and shared criteria used for the identification of malnutrition, frailty and sarcopenia there is still a lack of cohesive thinking around the overlap of applied definitions and identification criteria.

**Trial registration:**

ClinicalTrials.gov NCT04655456 approved on the 10th of December 2020.

## Background

The population around the world is ageing rapidly. It is expected that by 2050, the number of people older than 65 years worldwide will increase to two billion [1]. In England, the number of older people reached 18% of the population in 2016 [2]. Regardless of the decline in fertility and birth rates, all countries are experiencing an increase in life expectancy [3]. This increase has resulted in a rising demand for, and pressure on, local services. There is a particular demand for these services within the National Health Service (NHS) in the UK, where budget spending on older people grew from two percent to 16% between 2007 and 2016 [4]. Therefore, the health status of older members of the population is becoming a priority. A healthy dietary intake and active lifestyle are key components for healthy aging and are well recognised as factors associated with a lower risk of developing lifestyle-related diseases [5–7].

The aging process involves changes in body functions including alterations in the sense of smell and taste and capacity to chew and swallow [8]. These changes directly affect appetite and food intake [8], which can have an impact on nutritional status and can lead to malnutrition in the form of undernutrition [8]. There are two forms of malnutrition undernutrition, and being overweight or obese which results from diet-related non-communicable diseases [9, 10]. Cachexia is a another nutritional disorder which can be define as “a complex metabolic syndrome associated with underlying illness and characterized by loss of muscle with or without loss of fat mass” [11]. Malnutrition “undernutrition” is common in older people and generally increases with aging [12, 13]. It is crucial to detect malnutrition in older people because it causes a decline in overall health [14]. It can worsen the deterioration of health and functional status, and increase the risk of dependency and disability [12]. It is associated with undesirable health conditions, including an increased likelihood of morbidity and mortality [15, 16], an increased risk of falls [17], reduced cognitive function, and decreased bone mass in older people living in community dwellings [18, 19]. Furthermore, older malnourished inpatients have a higher number of complications and longer hospital episodes, which result in increased associated healthcare costs [10].

Over the last few decades, many criteria have been proposed for identifying malnutrition and many tools have been implemented. Most of these tools include a combination of the same variables or criteria: weight loss, body mass index (BMI) and signs of eating difficulties [20]. One of the most recently proposed definitions of malnutrition emerged from the Global Leadership Initiative on Malnutrition (GLIM). Here malnutrition is determined using a phenotype and aetiological model, which includes three phenotypes (non-volitional weight loss, low BMI and reduced muscle mass) and two aetiological criteria (reduced food intake and inflammation) [21]. The GLIM has broader criteria because it was developed using previous screening and assessment tools to ensure it is applicable in all countries and transferable to all settings. By using the GLIM criteria malnutrition can be compared in different settings through prevalence, incidence, intervention and outcome [21].

In addition to malnutrition, two other conditions frailty and sarcopenia are widespread in older populations. All three conditions are characterised with a loss of body tissue, which can result in negative outcomes such as an increased risk of falls [22], poor quality of life [23], increased risk of mortality [24, 25]. Malnutrition and frailty both have other similar characteristics in the assessments used, including, functional and cognitive status. Thus there is overlap in the definition and treatment of these conditions [26].

Frailty is associated with ageing and may lead to premature death [27, 28], multi-morbidity, specific long-term conditions and mortality [29, 30]. In addition, frailty has been shown to decrease the quality of life of older people [31]. It can be defined as a ‘state of increased vulnerability to poor resolution of homoeostasis after a stressor event’ [32]. Two of the most widely used models used to identify frailty are the phenotype model, which describes a group of patient characteristics [32], and the cumulative deficit model, which assumes an accumulation of deficits that happen with ageing [33, 34].

The phenotype model describes frailty as a ‘clinical syndrome in which three or more of the following criteria are present: unintentional weight loss (10 lbs in the past year), self-reported exhaustion, weakness (grip strength), slow walking speed and low physical activity’ [35]. This model is used as the definition to diagnose frailty in many studies [36].

The cumulative deficit model was proposed by Rockwood and Mitnitski and was validated in the Canadian study of Health and Aging [36, 37]. This model used an index that considers symptoms, signs, diseases and disabilities as deficits that are combined into an FI to determine frailty [38]. The original cumulative deficit model was based on 92 variables [39]. Subsequent research revealed that it could be reduced to 30 variables, without a loss in predictive validity [40]. The cumulative deficit model calculates the FI by defining the numbers of health deficits present in a person, and then dividing by the number of health deficits considered [38, 41].

In addition to malnutrition and frailty, the older adult population may also experience the related condition sarcopenia. In 2000, the World Health Organisation(WHO) estimated that 600 million people aged 60 or older worldwide were diagnosed with sarcopenia [42]. This number is predicted to increase to 1.2 billion by 2025, and to double by the year 2050 [42]. A study suggested that frailty and its relation to sarcopenia, malnutrition and other factors is a network called the ‘geriatric web of frailty’ [43]. It argued that frailty is a complex condition caused by many interacting factors, such as falls, fractures, impaired protein synthesis, malnutrition and sarcopenia [43]. Many researchers have shown that the overlap between frailty and sarcopenia is due to the shared features between them, such as weight loss and low physical capability. This is because both conditions involve a failure in skeletal muscle (low physical function) that is detected through grip strength and gait speed [35, 44].

People with sarcopenia have specific characteristics, including a low body weight and a deterioration in physical performance [45]. It can be defined as ‘a progressive and generalised skeletal muscle disorder that is associated with an increased likelihood of adverse outcomes including falls, fractures, physical disability and mortality’ [46]. Older adults with sarcopenia have reported poorer general health and physical function scores compared to participants without sarcopenia [45].

The European Working Group on Sarcopenia in Older People (EWGSOP) recommended criteria for diagnosing sarcopenia. These include low muscle mass, low muscle strength and lower physical performance [46]. In order to detect sarcopenia, two parameters are needed pertaining to the amount of muscle and its function. These can be translated into measurable variables: muscle mass, muscle strength, and physical performance [47]. To measure muscle mass, there are many techniques that could be used for assessment. These include computed tomography, magnetic resonance imaging, dual energy X-ray, and bioimpedance analysis [47]. The measurement of muscle strength has fewer validated techniques, and one of the most widely used is handgrip strength because it is easy to use and readily available [48]. Others include knee flexion or extension or peak expiratory flow. There are a number of methods that have been used for physical performance, including the short physical performance battery, gait speed, the timed get-up-and-go test and the stair climb power test [47]. However, the gait speed test is usually used for clinical practice and research [47].

There are different cut-off points when defining sarcopenia that are based on the measurement technique used and the availability of reference standards. The EWGSOP recommends the use of a reference value derived by calculating two standard deviations below the mean from data collected from healthy, young adults rather than other predictive reference population cut-off points [47].

The aim of this study is to explore the overlap between malnutrition, frailty and sarcopenia in an older population, using UK biobank data, by determining the estimated prevalence of these three conditions.

## Methods/design of UK Biobank

This is a cross-sectional study using participants recruited to the UK Biobank. The UK Biobank is a population-based prospective longitudinal cohort with information on approximately 500,000 people. Participants were recruited from the NHS aged between 40–69 years. However, the database included participants aged 37 to 73 for the baseline visit. Data were collected for the initial assessment visit between 2007 and 2010. This was termed the baseline assessment that will be used for this study. An invitation was sent by mail to people who were living within a reasonable travelling distance from the assessment centres used for data collection. People were recruited from England, Scotland and Wales.

At the baseline assessment visit, all participants had to be able to give consent before starting the assessment. Then a series of assessment stations where undertaken that included a touchscreen questionnaire and an interview questionnaire about diet, cognitive function, work history and digestive health [49]. In addition to demographic data, the participants were given cognitive function tests, their height, hip and waist measurements were recorded, as well as their bioelectrical impedance measurements and hand-grip strength. The UK Biobank database aims to improve prevention, diagnosis and treatment of a broad number of diseases. This detailed information on participants provides a resource for investigators to conduct research relating to particular diseases [49].

The UK Biobank Ethics and Governance Council (EGC) was founded by the Medical Research Council and Wellcome Trust, allowing them to act independently [50]. The UK Biobank controls all access to and use of the data [50]. However, UK Biobank evaluates all proposals to verify that they would be compliant with the participants’ consent and the Biobank’s Governance Framework and have received the required ethics approval [50]. The researcher and collaborators signed a Material Transfer Agreement (MTA) with the UK Biobank. The MTA was submitted and the payment process completed for the approved application, allowing the data to be released to the approved researcher.

### Eligibility and exclusion criteria

The participants included in the study will be both male and female, aged 50 years or older, who completed a touchscreen questionnaire, and physical measurements. Any participant who is under 50 will be excluded.

### Study sample size

This study will be a subset of the main sample size from the UK Biobank, and it is anticipated 381,000 participants will meet the inclusion criteria (76% of the total sample of participants in the UK Biobank, who met the inclusion criteria age 50 and above) [29].

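### The 381,000 is derived from age alone, and prevalence is divided by the total sample even though eligibility does not ensure that each condition can be classified

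*Protocol article*

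**What the plan says.** Three places in the protocol article describe the study sample.

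- Eligibility and exclusion criteria: participants are "aged 50 years or older, who completed a touchscreen questionnaire, and physical measurements". The only exclusion spelled out is age under 50.
- Study sample size: "it is anticipated 381,000 participants will meet the inclusion criteria", explained as "76% of the total sample of participants in the UK Biobank, who met the inclusion criteria age 50 and above". Methods/design of UK Biobank gives the cohort as holding "information on approximately 500,000 people".
- Abstract, Methods/design: "a subset of 381,000 participants: males and females aged 50 years and above who completed the baseline assessments".

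The Statistical analysis section obtains each prevalence by dividing the number identified with the condition by the total sample, and presents the overlap as Venn segments, each with a prevalence and confidence interval. Its last paragraph says that missing data in the condition-defining variables will be described, together with how the variables affect the results. It does not change the divisor.

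Under Mapping malnutrition to biobank variables, a case needs one phenotypic and one aetiological criterion. The aetiological criteria are reduced energy intake and inflammation by C-reactive protein (CRP). Table 2 gives the food frequency questionnaire and 24-hour recall as dietary sources.

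**The concern.** One number is given two bases. The sample size section derives it from age, while the abstract presents it as a count of people who also completed the assessments. Both cannot be right unless completion was essentially total, and the article does not say that it was.

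The headcount alone would change no result, because no power calculation rests on it. The denominator matters more. Prevalence and overlap are the main outputs, and the rule divides identified cases by everyone in the sample. A person without the data needed to settle a condition cannot enter the numerator but stays in the denominator, so an unknown status is treated as absence of the condition. CRP is the clearest example, as it is not named in the eligibility rule. Dietary intake is similar: a questionnaire touching on diet is part of the visit, but eligibility does not require that an energy intake be available.

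**Working it through.** **1. Reproduce the stated figure.** Inputs: 76% (Study sample size) and about 500,000 (Methods/design of UK Biobank).

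- 0.76 × 500,000 = 380,000, which agrees with 381,000 after rounding.
- 381,000 / 500,000 = 76.2%.
- 381,000 / 0.76 = 501,316, about the whole cohort.

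The figure is the age share of the full cohort, with nothing deducted for incomplete assessments.

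**2. Compare with eligibility.** The share is described as those "who met the inclusion criteria age 50 and above". Eligibility adds people "who completed a touchscreen questionnaire, and physical measurements". A group meeting all the conditions cannot exceed the group meeting the age condition alone, so on this derivation 381,000 is a ceiling.

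**3. How far below the ceiling?** The documents give no completion rate. For an assumed rate c among those aged 50 and above, N = 381,000 × c:

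| c (assumed) | N |
|---|---|
| 99% | 377,190 |
| 97% | 369,570 |
| 95% | 361,950 |
| 90% | 342,900 |
| 80% | 304,800 |

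At 97% or more the eligible number lies within 3% of the stated one.

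**4. Effect of the denominator rule.** Let N be the total sample, p the true prevalence in it, and u the share of true cases whose status cannot be determined. Identified cases number N·p·(1 − u), so

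estimate = N·p·(1 − u) / N = p·(1 − u).

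The relative shortfall is u. The documents give no value for u.

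In the Venn diagram, a true malnutrition case of unknown status drops out of every segment that includes malnutrition. If also frail and sarcopenic, that person moves from the three-way overlap into the segment for those two alone. Overlap involving malnutrition falls, and the segment without it gains.

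**5. Illustration only.** If u were 10%, 20% or 30% (assumed), estimates would be 0.90, 0.80 or 0.70 of the true value.

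**6. Precision.** The 95% half-width is 1.96 × √(p(1 − p)/n). At p = 5% it is 0.069 percentage points for n = 381,000, 0.077 for n = 304,800 (80%) and 0.083 for n = 266,700 (70%). Losing participants costs little precision, so the issue is bias.

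**The case against.** The strongest reply has four parts.

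- **The headcount is only anticipated and may be nearly right.** The questionnaire and measurements are stations of the baseline visit, so loss may be small, and the abstract may mean that completion is already reflected. This stands. A reader might infer that 381,000 is shown not to be the number meeting the inclusion criteria. The documents support only that its stated basis omits two of the criteria.
- **Nothing says that 381,000 itself will be the divisor.** This also stands. The rule refers to the people included at baseline, which is naturally the realised dataset. But the bias arises for any total that includes people of unknown status.
- **A missing component often leaves status settled.** Low BMI with raised CRP makes a malnutrition case even if diet is missing. No phenotypic criterion makes a non-case whatever the aetiological data. Normal muscle mass rules out sarcopenia, and three of five frailty items suffice. So a reader who takes an assumed 70–90% with all components and infers a 10–30% understatement is using an assumption-driven worst case that no figure in the documents supports. Settled non-cases, however, do not reduce u. Only settled true cases do.
- **Missing data are already covered, and flow counts belong in a fuller document.** The absence of a flow count is indeed no finding. But the article does state a denominator rule, and describing missing data does not alter it.

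**Conclusion.** The point holds in two parts of unequal weight.

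The smaller is an unreconciled basis for 381,000. It is derived from age alone, presented in the abstract as a count of completers, and set against an eligibility rule with further conditions. It is an upper limit on its own derivation, by an unknown and possibly trivial margin. The arithmetic itself is correct.

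The larger is the denominator. Dividing by the total sample counts people of undetermined status as non-cases and biases prevalence, and overlap involving the affected condition, downward. The direction follows from the stated rule, provided that some true cases lack the data needed to identify them. The size is the share of true cases so affected, which the documents do not give.

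**What to change.** 1. In the abstract and Study sample size, state that 381,000 is the age-eligible count before the completion criteria. If it is a count after them, say so and correct the derivation.
2. In Statistical analysis, replace the total sample as divisor with the participants whose status can be determined from the available data: for each condition separately, and jointly for all three in the Venn segments. Report these counts alongside the total.

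**Cost.** A few sentences and some counts, with somewhat smaller denominators and little loss of precision. The estimates then assume that people with a determinable status represent the rest, which should be reported with the missing-data description already promised.

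**One caution for malnutrition.** A non-case can be settled by the phenotypic items alone, but a case needs an aetiological item too, so the determinable group over-represents non-cases. Let f be the share with a phenotypic criterion, a the share of these with an aetiological one, and m the share with no aetiological data, unrelated to the rest. The true prevalence is f·a. The total-sample estimate is f·a·(1 − m), and the determinable-status estimate is f·a·(1 − m)/(1 − f·m). When f is small, these two are close. The estimate among people with all malnutrition components recorded should therefore be given beside it as a sensitivity analysis; under the same assumption it recovers f·a.

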### Baseline characteristics

Participant characteristics that will be recorded are detailed in Table 1.

**Table 1 pone.0278371.t001:** Baseline participant characteristics.

Variable	Data Description	Categories Description/Units of measurement
Age	reported in years	
Gender	male or female	
Smoking status	prefer not to answer, never, previous and current.	
Medications use	number of medications (treatments) were entered by participants in the questionnaire.	
Alcohol intake	Seven categories: daily, almost daily, three or four times a week, once or twice a week, one to three times a month, special occasions only, never and prefer not to answer.	
Education level	prefer not to answer, none of the above and other professional qualifications.	Other professional grouped: NVQ, HND, HNC or equivalent; CSES or equivalent; an O levels/GCSEs; an A levels/AS levels or equivalent; or a college or university degree
Occupation	Ten groups: manager and senior officials, professional occupations, associate professional and technical occupations, administrative and secretarial occupations, skilled trade occupations, personal service occupations, sales and customer service occupations, process plant and machine operatives, elementary occupations or other jobs	
Income	Seven groups: less than 18,000; 18,000 to 30,999; 31,000 to 51,999; 52,000 to 100,000; greater than 100,000; and the ‘do not know’ and the ‘prefer not to answer’ groups	Pounds sterling
Ethnicity	Eight categories: White, Mixed, Asian or Asian British, Black or Black British or Chinese; and another ethnic group, do not know, and prefer not to answer.	

NVQ = National Vocational Qualification, HND = Higher National Diploma, HNC = Higher National Certificate, CSES = Certificate of Secondary Education, GCSEs = General Certificate of Secondary Education or equivalent

At the baseline assessment participants’ medical histories were recorded including a list of comorbidities that is described as 43 long-term conditions similar to the Hanlon study [29]. In addition, we will include other characteristics as shown in Table 1.

#### Mapping malnutrition to biobank variables

The GLIM criteria will be applied to variables collected in the UK Biobank database in order to define participants with malnutrition. It includes five criteria, which will be mapped to equivalent variables that are available in the UK Biobank shown in Table 2.

**Table 2 pone.0278371.t002:** Variable mapped to malnutrition, frailty and sarcopenia.

Variable	Data Description	Categories Description/Units of measurement	Malnutrition	Frailty	Sarcopenia
Dietary intake	FFQ and 24-hour dietary recall		X		
Anthropometric measurements	height measured using a Seca 202 height measuring rod and weight measured using Tanita BC-418 MA body composition analyser	Height recorded in centimetre unit Weight recorded in kilograms unit	X	X	X
Body composition	Bioelectrical impedance using Tanita BC-418MA body composition analyser	used to determine body composition fat mass, fat-free mass and body water.	X	X	X
Handgrip strength	Jamar J00105 hydraulic hand dynamometer	Kilogram		X	X

These variables will represent three phenotypic criteria and two etiologic criteria, where patients will be defined as having malnutrition if they have one phenotypic criterion and one aetiological criterion. The three phenotypic criteria are BMI < 22 kg/m^2^ if participants are 70 years or older, or BMI < 20 kg/m^2^ if participants are under 70 years old [21]; weight loss, as reported by the participants’ response to ‘Compared with one year ago, has your weight changed?’; and finally fat free mass index, calculated by dividing fat free mass by height squared (FFMI, kg/m2). The thresholds will be <17 kg/m^2^ for males and < 15 kg/m^2^ for females [20].

The first etiologic criteria, is defined as reduced food intake < 50% reduction of the standard energy requirement for the male group (50–54 years: 2,581 kcal/day, 55–64 years: 2,581 kcal/day, 65–74 years: 2,342 kcal/day) and the female group (50–54 years: 2,103 kcal/day, 55–64 years: 2,079 kcal/day, 65–74 years: 1,912 kcal/day) [51]. The second etiologic criterion is inflammation based on the C-reactive protein (CRP). [11, 52].

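### The reduced-intake criterion for malnutrition is worded as a reduction of less than 50%, which read literally selects intake above half the requirement and excludes intake below it

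*Protocol article*

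**What the plan says.** The Background of the protocol article describes the malnutrition definition as having three phenotypes and "two aetiological criteria (reduced food intake and inflammation". The section on mapping malnutrition to Biobank variables makes this operative: "patients will be defined as having malnutrition if they have one phenotypic criterion and one aetiological criterion". Low intake or inflammation is therefore a necessary part of every malnutrition case.

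The same section then fixes the intake criterion. It "is defined as reduced food intake < 50% reduction of the standard energy requirement for the male group", with requirements for men of "50–54 years: 2,581 kcal/day, 55–64 years: 2,581 kcal/day, 65–74 years: 2,342 kcal/day" and for women of "50–54 years: 2,103 kcal/day, 55–64 years: 2,079 kcal/day, 65–74 years: 1,912 kcal/day". The second aetiological criterion is inflammation based on C-reactive protein (CRP). Table 2 gives the source of the intake data as "FFQ and 24-hour dietary recall".

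The article does not restate the intake threshold, convert it to kilocalories or work an example. The frailty index, by contrast, has both explicit inequalities and a worked example.

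**The concern.** The less-than sign is attached to a reduction, not to an intake. A small reduction is a near-normal intake, so the inequality as printed points away from the people the criterion is named for. It accepts mild shortfalls and rejects severe ones.

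If the sentence were coded as it stands, the intake arm of the malnutrition definition would select the wrong people. Malnutrition is one of the three conditions whose prevalence and overlap are the aim of the study. The error would pass into its crude and standardised prevalence and into the Venn segments that involve it. With an anticipated 381,000 participants, the confidence intervals would be narrow and would give no hint of the misclassification.

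**Working it through.** **Inputs from the article.** The operator and percentage (less than, 50%, applied to a reduction) and the six energy requirements, all from the section on mapping malnutrition. The article derives no figure from the threshold, so there is none to reproduce.

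**Step 1: translate the rule.** Reduction = 1 − intake / requirement. Then reduction < 0.50 is equivalent to intake > 0.50 × requirement.

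**Step 2: the dividing line in each group (0.50 × requirement).**

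| Group | Requirement (kcal/day) | Half (kcal/day) |
|---|---|---|
| Men 50–54 | 2,581 | 1,290.5 |
| Men 55–64 | 2,581 | 1,290.5 |
| Men 65–74 | 2,342 | 1,171 |
| Women 50–54 | 2,103 | 1,051.5 |
| Women 55–64 | 2,079 | 1,039.5 |
| Women 65–74 | 1,912 | 956 |

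**Step 3: apply three wordings to a man aged 50–64 (requirement 2,581 kcal/day).**

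| Intake (kcal/day) | Share of requirement | Reduction | Literal: reduction < 50% | Intake < 50% | Reduction ≥ 50% |
|---|---|---|---|---|---|
| 774 | 30% | 70% | not met | met | met |
| 1,265 | 49% | 51% | not met | met | met |
| 1,290.5 | 50% | 50% | not met | not met | met |
| 1,316 | 51% | 49% | met | not met | not met |
| 2,323 | 90% | 10% | met | not met | not met |
| 2,839 | 110% | −10% | met, unless some shortfall is required | not met | not met |

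The pattern is the same in all six groups. Among people eating less than their requirement, the literal rule selects the complement of those selected by a reduction of at least 50%. The two sensible wordings differ only at exactly 50%.

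**Step 4: illustrative size.** The article gives no distribution of intake. Assume, purely for illustration, that intake as a fraction of requirement is normal with mean 0.85 to 0.95 and SD 0.27.

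- P(intake < 0.50) = Φ((0.50 − 0.85)/0.27) = Φ(−1.296) = 0.097, and Φ((0.50 − 0.95)/0.27) = Φ(−1.667) = 0.048.
- P(0.50 < intake < 1.00) = Φ(0.556) − Φ(−1.296) = 0.613, and Φ(0.185) − Φ(−1.667) = 0.526.
- P(intake > 0.50) = 1 − 0.097 = 0.90, and 1 − 0.048 = 0.95.

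Under these assumptions the literal rule is met by about 53–61% if some shortfall is required, or 90–95% if intake at or above the requirement also counts. Intake below half is met by about 5–10%.

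**The case against.** The best defence is that this is garbled wording and not a chosen rule. The phrase uses the idea of reduction twice. The criterion is named for reduced intake, and the BMI and fat-free mass index thresholds in the same section put the measured quantity to the left of the less-than sign, where food intake stands here. The requirements are given as the base of which 50% is taken. These cues favour intake below 50% of requirement, and the analysts may well have coded that. This stands as the likely explanation. It does not rescue the sentence, because the printed threshold gives the wrong classification when followed and nothing else in the article corrects it.

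A reader might also infer three stronger things that the article does not support.

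- **That malnutrition collapses to having any phenotypic criterion.** That needs people eating at or above their requirement to count as having reduced intake, which contradicts the criterion's name. If some shortfall is required, the illustration leaves about 39–47% not flagged on intake, and they would still need to qualify through CRP.
- **That malnutrition prevalence and every Venn segment containing it would be inflated by a known amount.** The literal rule adds some people and removes others. The net effect depends on how intake, CRP and the phenotypic criteria occur together, which the article does not report.
- **That the rule contradicts every meaning of reduced intake.** An intake at 60% of requirement is reduced. The fault is that the larger reductions are excluded.

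**Conclusion.** The point holds as an error in the operative wording of a case definition. Read literally, the criterion is met by intake above half the requirement and not met by intake below it. This follows from the printed words alone and needs no assumption. Coded that way, everyone below half the requirement would be missed unless CRP qualified them, and everyone between half and the full requirement would be flagged.

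The effect on malnutrition prevalence and on the overlap segments cannot be computed from the article. The contrast of about 53–61% with about 5–10% is for the intake criterion alone. It rests on an assumed normal distribution, an assumed mean range and a single assumed SD, so it should be read only as a sign that the difference could be large. Whether the analysis code contains the inversion is unknown.

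**What to change.** Restate the criterion with one quantity and one operator, for example: *reported energy intake below 50% of the age- and sex-specific standard requirement*. Confirm that this wording, and the handling of an intake at exactly 50%, match the cited criterion and the analysis code. Printing the half-requirement values is optional, since they follow from the requirements already listed.

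The cost is one sentence and a check of one line of code. If the code turns out to follow the literal wording, the malnutrition classification and the results built on it would need to be rerun.
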